## Abstract

**Background:**

Despite the promise and popularity of advance care planning, there is insufficient evidence that advance care planning helps patients to meet their end-of-life care preferences, especially in Asian settings. Thus, the proposed study aims to assess whether patients with advanced heart failure who are receiving advance care planning have a greater likelihood of receiving end-of-life care consistent with their preferences compared to patients receiving usual care. Secondary objectives are to compare differences in health care expenditures, quality of life, anxiety and depression, understanding of own illness, participation in decision-making and concordance with their caregiver’s preferences for end-of-life care, between patients with advanced heart failure receiving advance care planning and usual care.

**Methods/design:**

This is a two-arm randomized controlled trial of advance care planning versus usual care (control) conducted at two institutions in Singapore. Two hundred and eighty-two patients with advanced heart failure (*n* = 94 in the advance care planning arm; *n* = 188 in the control arm receiving usual care) will be recruited from these centers and followed for 1 year or until they die, whichever is earlier. Additionally, the study will include up to one caregiver per patient enrolled.

**Discussion:**

If advance care planning is proven to be effective, the results will help to promote its uptake among health care providers and patients both within Singapore and in other countries.

**Trial registration:**

NCT02299180. Registered on 18 November 2014.

## Background

Worldwide there is an increasing awareness of inadequacy in end-of-life (EOL) care provided to patients with non-cancer-related terminal illnesses, such as advanced congestive heart failure (CHF) [1]. Data from several countries shows that despite therapeutic advances and high health care expenditures [2], patients with advanced CHF suffer enormously from the physical and psychological effects of their illness [3–5]. Unlike many patients with advanced cancer, patients with CHF typically experience a gradual but non-linear decline in physical function over many months or years, with occasional periods of exacerbation [6]. The non-linear deterioration in health leads to difficulties in prognostication and often delayed referral to specialist palliative care services. Moreover, there is evidence that patients’ understanding of their illness is often poor and communication with their physician inadequate [7, 8]. These concerns suggest that patients may be receiving suboptimal EOL care that is not consistent with their preferences and receiving EOL care that may involve disproportionately large health care expenditures.

There is increasing evidence that the presence of advance directives alone does not help in meeting patient preferences or in reducing aggressive treatments and cost of care [9–13]. In contrast, advance care planning (ACP), one of the most widely discussed and studied of all EOL conversations, is believed to enable patients to meet their EOL preferences. This is because ACP is an ongoing process by which the patient, in consultation with health care providers and/or family members/caregivers, makes decisions about their future health care should they become incapable of participating in medical treatment decisions. Further, it shifts the focus on EOL decision-making away from completion of documents and towards facilitating discussion about values and preferences regarding treatment and care, and involves family members in the discussion [9].

Despite the promise and popularity, there has been little research evaluating the effectiveness of ACP in meeting patient preferences, especially in Asian settings. One randomized controlled trial (RCT) of the “Respecting Choices” model for ACP, among elderly hospitalized patients in Australia, has reported positive outcomes in enabling people to receive EOL treatment as per their wishes [14]. Another controlled trial, conducted in a nursing home in the US also found higher compliance with patients’ wishes among those receiving ACP [15]. An RCT by Kirchhoff et al. [16] among individuals with CHF or end-stage renal disease failed to show any significant difference in the proportion of patients who met their preferences regarding cardiopulmonary resuscitation (CPR) between the ACP and control arms. Thus, there has been mixed evidence regarding the effectiveness of ACP, with none from an Asian setting.

This study aims to fill this gap. It is a two-arm RCT of patients with advanced CHF to assess the impact of ACP on health and cost outcomes. The study will be conducted in Singapore, a rapidly aging country in Southeast Asia. We will survey the patients in both arms every 4 months for a period of 1 year or until they die, whichever is earlier. The primary objective of this trial is to assess whether patients receiving ACP have a greater likelihood of receiving EOL care consistent with their preferences compared to patients receiving usual care. Secondary objectives are to compare heath care expenditures, quality of life, anxiety and depression, understanding of own illness, participation in decision-making and concordance with caregiver preferences for EOL care between patients receiving ACP and usual care. We hypothesize that patients receiving ACP will be more likely to receive EOL care consistent with their stated preferences, and have lower health care expenditures, better quality of life, lower anxiety and depression, better understanding of their own illness, greater participation in decision-making, and greater congruence with caregiver preferences, as compared to patients receiving usual care.

## Methods/design

### Study design

This is a two-arm RCT of ACP versus usual care conducted at two institutions in Singapore –the National Heart Centre Singapore and Singapore General Hospital (Department of Internal Medicine). The two hospitals were chosen because they are the largest centers/hospitals that currently have trained ACP facilitators to deliver ACP to patients with advanced CHF. All ACP facilitators in Singapore are trained based on similar principles and with similar intensity and methodology. Therefore, the study results are likely to be generalizable to patients with advanced CHF who are receiving ACP at any hospital in Singapore.

Two hundred and eighty-two in-patients with advanced CHF (*n* = 94 in the ACP arm; *n* = 188 in the control arm receiving usual care) will be recruited from these centers and followed for 1 year or until they die, whichever is earlier. Additionally, the study will include up to one caregiver per patient enrolled.

Randomization will follow a 1:2 (ACP: control arm) ratio. The unequal number of patients in the ACP and control arms is because it was anticipated that over the course of the study duration, due to increasing popularity of ACP in Singapore, many patients in the control arm may decide to take up ACP, thus contaminating the control arm. If this happens, the larger number of participants in the control group is expected to increase the statistical power for a “per-protocol” analysis [17].

### Study population

The study will recruit patients with advanced CHF (New York Heart Association classes III and IV) while they are hospitalized, who are 21 years and older and able to give informed consent. Those with psychiatric or cognitive disorders, a previously documented ACP or those who have undergone ACP facilitation will be excluded. The study protocol has been approved by the Institutional Review Board at Singhealth.

### Intervention

The patient and their family members will be referred to an ACP facilitator. The ACP facilitator will be certified in providing ACP. Other than assisting individuals in determining their preferences for future medical care, the ACP facilitator will provide emotional support to patients/families with making EOL decisions. Family members will be encouraged to be present during the ACP discussion so that the whole family unit will be able to explore goals, values and beliefs towards the patient’s medical care. With family members’ participation, there is a greater likelihood that they come to understand and support the decisions made by the patient during ACP. Patients will be encouraged to appoint a substitute health care decision-maker who will make the decisions on their behalf when they are no longer able to do so.

The ACP document is dated and specifies whether the patient prefers CPR or not, and whether the patient wants comfort measures only (medications, oxygen and other measures may be used for comfort at the place where the patient lives), limited additional intervention (may include limited trial of treatment, oral/intravenous medications, non-invasive ventilation support and transfer to hospital, if needed) or full treatment (may consider intubation, mechanical ventilation, cardioversion and transfer to intensive care, if needed) as well as any other additional care preferences. Preferred place of medical treatment in the event of deterioration as well as preferred place of death is also noted in the ACP document. The names of substitute decision-makers are specified. A copy of the completed ACP document will be provided to the patient, substitute health care decision-makers and the health care team. The ACP document will be filed onto the front page of the patient’s inpatient case notes and a copy will be scanned into the patient’s electronic medical records in the National IT System, which is shared by all hospitals in Singapore, for easy retrieval and viewing in case the patient is admitted to any hospital in Singapore. This is to ensure that immediate retrieval of the ACP document is possible when treatment decisions must be made quickly.

Patient preferences among those in the intervention arm will be reviewed periodically upon readmission or during the outpatient clinic by the ACP facilitator. If the patient expresses different preferences towards future medical care, then the ACP facilitator will conduct a session as soon as possible to explore the updated goals for the patient’s current medical preferences and the existing ACP document will be voided. If the patient has a change of mind towards future medical care in between visits, then the patient will be encouraged to contact the ACP facilitator in charge via phone of their change in mind. The ACP facilitator will then arrange for a session as soon as possible to explore the patient’s wishes and update the ACP document.

### Control arm

The control arm patients will not take part in ACP discussions and documentation, but will continue to receive usual care.

### Outcome measures

#### Primary outcome

The primary outcome to be assessed in the study is the proportion of patients receiving EOL care consistent with their stated preferences. Patients’ stated preferences for CPR, life-prolonging treatments (comfort measures only/limited intervention/full treatment), place of care and place of death will be assessed from their last survey or their ACP document. The actual treatment received by the patient will be assessed from their medical records after the patient’s death. If these records are unavailable, this information will be assessed in post-death interviews with the patient’s family members/surrogate decision-maker. Actual place of death will be ascertained from death certificates and actual place of care from post-death interviews with the patient’s family members/surrogate decision-maker. The analysis will only be conducted for the sub-group of patients who die during the study period.

Secondary outcomes:Heath care expenditures during study duration: inpatient costs will be assessed through linkages with hospital billing recordsPatients’ quality of life: patients’ quality of life will be measured through Kansas City Cardiomyopathy Questionnaire (KCCQ). The KCCQ is a 23-item questionnaire that quantifies physical limitations, symptoms, self-efficacy, social interference and quality of life for patients with CHF [18]. This scale will be administered both during baseline and follow-up surveyPatients’ anxiety and depression: we will assess patients’ anxiety and depression through the Hospital Anxiety and Depression Scale (HADS) [19, 20]. HADS is an extensively used, valid and reliable scale to measure anxiety and depression among patients in non-psychiatric hospital clinics. It has two subscales – an anxiety subscale (HADS-A) and a depression (HADS-D) subscale, with a total score ranging from 0 to 21 for each. Internal consistency (Cronbach’s alpha) for HADS-A varies from .68 to .93 and for HADS-D from .67 to .90. An optimal balance of sensitivity and specificity is achieved by a score of 8 or above on both HADS-A and HADS-D. The sensitivity and specificity for both HADS-A and HADS-D is 0.80 [19]. These scales will be administered during the baseline interview and during follow-up surveys with the patientPatients’ understanding of own illness: understanding of illness will be assessed by asking patients whether they thought that their current treatments would help them to live longer (yes/no/unsure), cure their heart condition (yes/no/unsure) and relieve their symptoms (yes/no/unsure)Patients’ participation in decision-making: patients’ participation in decision-making will be measured by the Decisional Conflict Scale [21] administered at baseline and in follow-up surveys. The Decisional Conflict Scale measures patient’s state of uncertainty about the course of action to take. This state is likely to occur when making choices involving risk or uncertainty of outcomes and the need to make tradeoffs in selecting a course of action (e.g., when making decisions regarding EOL treatment and care). The scale’s internal consistency ranges from 0.78 to 0.92 and the test-retest reliability coefficient is .81 [21]. It has also been used and validated among cancer patients [22]Patient and caregiver congruence in EOL preferences: for patients whose caregivers also consent to participate in the survey, we will assess their preferences for patient’s EOL care – CPR, life-prolonging treatments and place of death

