### Limitations

Attrition may be a problem. We will try to minimize this through appropriate patient incentives and by scheduling interviews at times and places convenient for patients. It is also not possible to execute a double-blinded trial of ACP given that ACP is provided by a multidisciplinary team. Unblinded trials may be prone to bias, such as in assessment of primary outcome. We will attempt to reduce subjectivity in assessment of the outcome by having more than one senior investigator in the study team to review the contents of the medical records and to assess compliance with patients’ wishes as stated in the ACP or the survey documents. Contamination of the control arm is also possible if patients in the control arm seek ACP outside of the trial, during the follow-up phase.

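### The primary outcome may take the stated preference from either the survey or the ACP document, with no rule for which counts, and only the ACP arm has an ACP document by design

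*Protocol article*

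**What the plan says.** The endpoint is "the proportion of patients receiving EOL care consistent with their stated preferences", analysed among patients who die. For the preference side of that comparison, the Primary outcome section names two sources joined by an unqualified alternative: "place of care and place of death will be assessed from their last survey or their ACP document". The Limitations section repeats the alternative for the outcome assessors, who review the records "to assess compliance with patients’ wishes as stated in the ACP or the survey documents". That section also concedes that the trial cannot be double-blind and that assessment of the primary outcome is open to bias.

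The two sources are not equally available:

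- Survey, both arms: "We will survey the patients in both arms every 4 months for a period of 1 year or until they die, whichever is earlier" (Background).
- ACP document, ACP arm: "Patient preferences among those in the intervention arm will be reviewed periodically upon readmission or during the outpatient clinic by the ACP facilitator" (Intervention). When wishes differ, the existing document is voided. A patient who changes their mind between visits is encouraged to telephone the facilitator.
- ACP document, control arm: "The control arm patients will not take part in ACP discussions and documentation, but will continue to receive usual care" (Control arm). The exception is a control patient who obtains ACP outside the trial, which the Limitations section foresees.

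The ACP document also guides care: "The ACP document will be filed onto the front page of the patient’s inpatient case notes" (Intervention).

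**The concern.** Concordance compares care received with a recorded wish. If the recorded wish comes from a different instrument in each arm, the arms can differ because of the record and not the care. Here the possible sources differ in three ways:

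- **Elicitation:** a facilitated discussion, with family encouraged to attend, against a research questionnaire.
- **Updating:** review at readmission or clinic, or after a call, against a 4-monthly visit.
- **Independence:** the ACP document is itself what the treating team reads.

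A change of wishes between surveys can move the yardstick for an ACP patient but not for a control patient. An ACP patient may also have two records that disagree. Nothing then stops an assessor who knows the arm from choosing between them. Having more than one senior investigator review the records reduces subjectivity in judging care, but it does not supply a common reference.

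The benefit of ACP in helping clinicians follow a patient's wishes is a real effect and should count. The problem is only the part of any difference that comes from how, and how recently, the wish was recorded.

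**Working it through.** **Plan's own figure.** Inputs from the Sample size section are 65% against 15%, 90% power and 95% certainty (read as two-sided 5%). Allocation is 1:2. The pooled proportion is (0.65 + 2 × 0.15)/3 = 0.317. Without continuity correction, ACP-arm deaths = [1.960·√(0.317 × 0.683 × 1.5) + 1.282·√(0.65 × 0.35 + 0.15 × 0.85/2)]² / 0.50² = 13.1, so 14, with 28 control deaths. At 15% mortality, 14/0.15 = 93.3, so 94 patients and 2 × 94 = 188. The stated size reproduces and is not in dispute.

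**Assumptions for the bias.** The documents give no preference stability and no age of records at death, so all of the following are assumed:

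- True concordance with the current wish is q in both arms.
- The preference is binary and changes with probability m per month, and it can change back.
- A record t months old matches the current wish with probability s = [1 + (1 − 2m)^t]/2.
- Measured concordance is q·s + (1 − q)(1 − s) = 0.5 + (q − 0.5)(1 − 2m)^t.
- The ACP document is 1 month old. The survey is 4 months old (the oldest an on-schedule survey can be) or 2 months old (the average if deaths fall evenly between surveys).

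The false gap, ACP minus control, is (q − 0.5)·[(1 − 2m) − (1 − 2m)^t]. For example, with q = 0.70, m = 0.10 and t = 4, it is 0.20 × (0.800 − 0.410) = 0.078.

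| True concordance | Survey age | m = 3% | m = 5% | m = 10% |
|---|---|---|---|---|
| 70% | 4 months | +3.2 | +4.9 | +7.8 |
| 70% | 2 months | +1.1 | +1.8 | +3.2 |
| 15% (plan's control rate) | 4 months | −5.6 | −8.5 | −13.7 |
| 15% | 2 months | −2.0 | −3.2 | −5.6 |

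(Percentage points. Positive favours ACP.)

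The sign reverses below 50% because a stale binary record then matches the care received by chance more often than a current one does.

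**Effect on the test.** These are exact binomial enumerations at 14 and 28 deaths, two-sided 5%.

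- Largest 4-month gap at 70% (66.0% against 58.2%): rejected 8.5% of the time by chi-square and 6.3% by Fisher.
- Largest 2-month gap at 70% (66.0% against 62.8%): 6.0% and 4.2%.
- Equal rates of 58% to 66%: 5.5% to 6.0% and 3.6% to 3.9%.

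**A different scoring model.** Suppose that a record not matching the current wish always scores as discordant, and that true concordance is 65% in both arms. The gap then always favours the arm with the more accurate record.

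- Record accuracy 95% (ACP) and 80% (survey): 0.65 × 0.95 = 62% against 0.65 × 0.80 = 52%, rejected 10.6% (chi-square) or 7.5% (Fisher).
- Record accuracy 100% and 70%: 65% against 46%, rejected 25.2% or 19.1%.

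Size and direction therefore both turn on figures that the protocol does not supply.

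**The case against.** **Both arms have the survey.** A reader might infer that each arm is tied to its own source. The text does not say so: ACP patients answer the same surveys. The defect is the unresolved choice of source. An unshown full protocol or SAP might resolve it, but this is the definition of the primary endpoint, and as published it permits ascertainment that depends on arm.

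**ACP documents need not be fresher.** The first meeting is within 48 hours of consent and later review is only periodic, so an unrevised document can be older than the last survey. This stands. A reader might infer that the bias must favour ACP. The documents do not support that, and under the binary model it fails below 50% true concordance.

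**Surveys in an extension.** A reader might infer that control preferences would go unrefreshed for up to a year if follow-up is extended, because the Background limits surveys to 1 year. The Recruitment and data collection section, however, mentions possible further follow-up and then gives 4-monthly interviews with no end date. The Sample size section also speaks of further follow-ups. The wording needs reconciling; it does not establish that surveys stop.

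**Eliciting and updating wishes is the intervention.** Scoring on the survey alone can count as discordant an ACP patient who was treated according to a newer, valid document. This stands as a cost. It includes ACP patients who die before the first follow-up survey, whose only survey was completed before randomisation. If deaths fell evenly over the year, that would be 4/12, or a third of them.

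**Conclusion.** The point holds as a defect in the definition of the primary outcome. The reference standard may differ by arm, and no rule prevents it. Under the binary model, with 70% true concordance and 3% to 10% monthly change, the false gap is about 3 to 8 points for a 1-month-old document against a 4-month-old survey. Against a 2-month-old survey it is about 1 to 3 points, which hardly moves the false-positive rate. The sign is not fixed. A reader might infer that the planned effect could be an artefact of measurement; no gap computed here, under either scoring model, reaches the planned 50 points. The reason to act is that the flaw sits in the primary endpoint, assessment is not blinded, and a source chosen after outcomes are known would not be credible.

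**What to change.** Settle the following in the protocol or SAP before any outcome is adjudicated:

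1. Define the primary preference in both arms as the last completed study survey before death, using the same items.
2. Use the ACP document, or the most recent record of either kind, only in a labelled sensitivity analysis.
3. Report the interval from recorded preference to death by arm.
4. Reconcile the 1-year limit in the Background with the Recruitment and data collection and Sample size sections, so that it is clear the 4-monthly survey continues in both arms during any extension.

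The cost is a change of wording, plus a few more interviews if follow-up is extended. The surveys are already planned in both arms, and 14 and 28 deaths and 94 and 188 patients stand. The downside is that some ACP patients whose care followed a newer document will score as discordant in the primary analysis. The sensitivity analysis will show how many, and the two should be reported side by side.

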
### Recruitment and data collection

A list of patients with heart failure who are admitted at each center will be sent to the research team daily by heart failure nurses/research coordinators from these centers. The research team will then screen the list for eligibility criteria and approach the patient and family members for participation in the study; those agreeable to participate will be administered a written informed consent form and administered the baseline survey.

Eligible patients who consent to participate in the RCT and answer the survey questionnaires will be randomized to the ACP and control arms. Participants who are randomized into the intervention (ACP) arm will meet with ACP facilitators within 48 hours of consent for intervention delivery. Patients randomized to the control arm will not take part in ACP discussions and documentation, but will continue to receive usual care.

Randomization will be done using block randomization by generating a random allocation sequence of participants to the intervention and control arms through a computerized random number generator. This will be done by a statistician at the institution. The allocation will be concealed in sequentially numbered, opaque and sealed envelopes by the data manager and given to the research coordinator conducting patient recruitment at the two centers. Envelopes will be opened sequentially by the research coordinator only after the participant unique ID is written on the envelope. Randomization sequence will not be known to the research coordinator, health care providers (physicians, ACP facilitators, heart failure nurses) and other researchers involved in the study.

Patients will be followed by the research team for 1 year or until death, whichever is earlier. Further follow-up may be needed if the targeted number of deaths in the intervention and control arms is not reached within the 1-year follow-up period. Patients will be interviewed first at baseline and then every 4 months. At the end of the follow-up period, their medical and billing records will be reviewed to assess the treatment they received and related costs. All questionnaires for both patients and caregivers will be administered in their preferred language from a selection of four: English, Mandarin, Malay, and Tamil. If the patient dies during the study, consenting caregivers will be asked to complete a post-death questionnaire (Fig. 1).

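### Actual place of care, one of four primary-outcome domains, is taken only from post-death family interviews although records are reviewed anyway, leaving it open to missing data and arm-dependent reporting

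*Protocol article*

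**What the plan says.** All of this is in the protocol article.

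- **Domains.** The Primary outcome section lists preferences for resuscitation, life-prolonging treatment, place of care and place of death. On the preference side, "place of care and place of death will be assessed from their last survey or their ACP document".
- **Sources for what actually happened.** Treatment comes from medical records, with a fallback: "If these records are unavailable, this information will be assessed in post-death interviews". Place of death comes from death certificates. For place of care the text gives "actual place of care from post-death interviews" with family members or the surrogate decision-maker, and no second source.
- **Who is interviewed.** Under Study design, "the study will include up to one caregiver per patient enrolled". Under Recruitment and data collection, if the patient dies, "consenting caregivers will be asked to complete a post-death questionnaire".
- **Records in hand.** The same section says that at the end of follow-up "their medical and billing records will be reviewed to assess the treatment they received and related costs".
- **Family exposure to the intervention.** Under Intervention, "Family members will be encouraged to be present during the ACP discussion", and substitute decision-makers receive a copy of the completed document. Control patients have no such discussion or document.
- **Safeguard.** Limitations accepts that lack of blinding may bias assessment of the primary outcome. The answer given is that more than one senior investigator reviews the medical records.

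**The concern.** The plan sets a sensible source order for treatment received and then departs from it for place of care, where the interview stands alone. That has two consequences.

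First, a decedent with no interviewed relative has no stated source for this domain. Enrolling a caregiver is optional and the questionnaire depends on consent, so some gaps should be expected. Willingness to be interviewed may differ between families who took part in ACP and families who did not.

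Second, the informants are not neutral between arms. An ACP-arm relative may have sat in the discussion and hold the written preference; a control relative has had neither through the trial. Recall of where care took place can lean towards the known wish in one arm only. The safeguard in Limitations acts on the record review and so does not reach a domain that comes from interviews.

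The comparison is planned on 14 and 28 deaths, which leaves little room for lost or distorted data in any domain.

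**Working it through.** **1. The four steps side by side**

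| Item | First source | Fallback | Covered by multi-reviewer safeguard? |
|---|---|---|---|
| Treatment received (including resuscitation) | Medical records | Interview | Yes, when from records |
| Place of death | Death certificate | None stated | Not needed in the same way |
| Place of care | Interview | None stated | No |

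Place of care is the only domain for which a relative's report is the sole source.

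**2. The plan's own sample size**

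Inputs from Sample size: 65% (ACP) against 15% (control), power 90%, and 95% certainty, which I read as two-sided alpha 0.05. Allocation is 1:2 (Study design).

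Pooled-variance formula with ratio r = 2:

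n(ACP) = [z(0.975)·√(p̄(1−p̄)(1+1/r)) + z(0.90)·√(p1(1−p1)+p2(1−p2)/r)]² / (p1−p2)²

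- p̄ = (0.65 + 2×0.15)/3 = 0.3167
- n = (1.1166 + 0.6916)² / 0.25 = 13.08, rounded up to 14; control 28
- Patients at 15% mortality: 14/0.15 = 93.3, so 94; 2×94 = 188

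The stated 14/28 deaths and 94/188 patients reproduce, so the arithmetic is not at issue.

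**3. Missing interviews (conditional illustration)**

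Assumptions: 10%, 20% or 30% of decedents have no interview, and such a decedent is left out of the primary test. The document gives neither the rates nor that rule. Power is by exact enumeration of the two binomials at 65% against 15%, two-sided 0.05.

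| Lost | Scored deaths (ACP/control) | Fisher | Chi-square |
|---|---|---|---|
| 0% (plan) | 14/28 | 88% | 92% |
| 10% | 13/25 | 85% | 90% |
| 20% | 11/22 | 79% | 86% |
| 30% | 10/20 | 77% | 82% |

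The loss should be read against the first row: about 2 to 3 points at 10% missing, 6 to 9 at 20%, and 10 to 11 at 30%.

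**4. Arm-dependent reporting (illustration, place-of-care domain only)**

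Assumptions: no true difference, and a fraction m of truly discordant cases reported as concordant in the ACP arm, none in control.

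Observed ACP rate = p + m(1−p).

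- p = 0.40, m = 0.20: 0.40 + 0.20×0.60 = 0.52, a false difference of 12 points. Probability of rejecting at 14/28: Fisher 3.8% without misreporting, 9.2% with it (chi-square 5.9% and 13.5%).
- p = 0.40, m = 0.10 or 0.30: observed 0.46 or 0.58; Fisher 5.1% or 16.5%.
- p = 0.15 (the plan's control rate for the overall outcome, borrowed here), m = 0.20: 0.15 + 0.20×0.85 = 0.32; Fisher 2.5% without misreporting, 19.9% with it.

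**The case against.** There is a plain reason to ask the family. Patients may prefer care where they live, and the billing linkage described under Secondary outcomes covers inpatient costs. Hospital records show admissions; they do not reliably show care at home or in the community. This stands, and it is why the interview should be kept as a source and not dropped.

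A reader might infer that a missing interview makes the whole primary outcome unscorable. The document does not support that. It nowhere says that the four domains form a composite, or that a decedent lacking one is excluded. Proposed statistical analysis names kappa for place of death and each life-sustaining treatment and does not mention place of care there. If the domains are analysed separately, a missing interview costs nothing on the other three.

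A reader might also infer that patients without an enrolled caregiver have no informant. The Primary outcome section speaks of family members or the surrogate, which may reach beyond the enrolled caregiver. The consent wording under Recruitment and data collection is narrower, so gaps are likely, but their extent is unknown.

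Where care took place is a fairly factual item, and the relative does not judge concordance. One-arm misreporting of 20% is an assumption, and its effect would be diluted in any measure across domains.

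Finally, moving to records does not blind anyone. The ACP document is filed at the front of the inpatient notes and scanned into the electronic record, so record reviewers can also see the arm and the wish. This too stands: the change reduces reliance on relatives' reports without removing knowledge of allocation.

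**Conclusion.** The point holds as a weakness in a stated measurement choice, worth correcting. It is not an arithmetic error and not a detail that the article merely leaves to a fuller document: the source for place of care is fixed, it is the interview alone, and it departs from the order used for treatment received while relevant records are already being reviewed.

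The established part is qualitative: this domain may be missing for some decedents, response and reporting can differ by arm, and the stated safeguard does not cover it. That ACP-arm informants know the arm is inferred from the Intervention and Limitations sections; nothing says that informants are blinded.

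The size is illustrative only. The fall in power from 88% to between 85% and 77% (Fisher) needs both an assumed 10% to 30% loss and an exclusion rule that the document does not contain. The rise in false rejection from about 4% to 9% applies to place of care alone and rests on assumed misreporting of 20% in one arm and a true rate of 40%.

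**What to change.** Change the source rule for actual place of care in the Primary outcome section, identically in both arms:

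1. Take hospital, intensive-care and other inpatient place of care from the medical and billing records already under review.
2. Use the post-death interview for care at home or in the community, and wherever the records are silent.
3. Report by arm how many decedents were classified from records, from interview, or not at all.

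The cost is a change of wording and one more item on the existing abstraction form; no new data source is needed. Record coverage of community settings will remain incomplete, so some dependence on relatives stays. Reviewers will still not be blind to arm, but the record-based part of this domain would come under the multi-reviewer check that Limitations already provides.
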